### 2.4. Outcomes

The primary outcome parameters of the INSIC trial are as follows:
(1)The incidence rate of SIC within a 14-day observation period (new cases/1000 patient days).(2)The point prevalence of SIC on day 1 of the study period and on three reference days in the 4th quarter of each year from 2019 to 2023.

The secondary outcome parameters of the INSIC trial are as follows:
(1)Length of stay in the ICU until transfer to a normal ward.(2)ICU mortality rate (in all patients and in the subgroups of patients with sepsis, septic shock, SIC, or SAC (mild, moderate, severe) according to the different scores).(3)Mortality rate until day 28, hospital death, or hospital discharge (whatever occurs first, in all patients and in the subgroups of patients with sepsis, septic shock, SIC, or SAC (mild, moderate, severe) according to the different scores).(4)SIC and SAC (mild, moderate, severe) recovery rate 72 h after SIC or SAC onset. The time point was chosen as the 72 h period reflects a critical window during which early death in sepsis or a clinical response to sepsis therapy can be expected [15].(5)Thromboembolic events after sepsis onset (in sepsis, septic shock, SIC, or SAC (mild, moderate, severe)) up to day 28, death, or hospital discharge (whichever occurs first).(6)Relevant bleeding without surgical trauma (hemoglobin loss >1 g/dL within 24 h, due to bleeding rather than dilution) after sepsis onset (in sepsis, septic shock, SIC, or SAC (mild, moderate, severe)) until day 28, death, or hospital discharge (whichever occurs first).

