For each patient diagnosed with sepsis or septic shock during the observation period, more detailed information will be collected (date and time of sepsis onset, date and time of septic shock onset, infectious focus, causative pathogen(s), and secondary infections (super- and/or nosocomial infections and/or infections of a further organ system)). Furthermore, investigators will be asked to extract data from the hospital information system describing additional patient characteristics. These include the American Society of Anesthesiologists (ASA) classification [16], the Revised Cardiac Risk Index (RCRI) [17] score, the status of and, if applicable, the reason for pre-existing anticoagulation therapy or antiplatelet therapy, coagulopathy, and severe liver disease. Furthermore, information on past episodes of heparin-induced thrombocytopenia (HIT) type II will be collected. For all patients hospitalized with sepsis in the ICU on the first day of the observation period, it will be determined whether SIC was present before the start of the observation period. Furthermore, for each patient diagnosed with sepsis or septic shock during the observation period, on the day of sepsis diagnosis (day 0), on days 1–4, and on the day of sepsis discharge, the following measures will be collected: the sequential sepsis-related organ failure assessment (SOFA) score [2], the international normalized ratio (INR), and platelet count. For further exploratory analyses, the following parameters are recorded where available: anti-factor Xa activity, activated partial thromboplastin time (aPTT), prothrombin time, D-dimer level, fibrinogen concentration, thrombin–antithrombin complex (TAT) concentration, thrombin fragment F1.2 concentration, and measures from thrombelastometric testing. Likewise for exploratory analyses, the following parameters are collected: the levels of inflammation markers (C-reactive protein (CRP), procalcitonin (PCT), and interleukin-(IL) 6), as well as the dose of anticoagulant administered, the amount of fluid infused (per day), the amount of blood products transfused (per day), and the administered amount of coagulation factors and desmopressin (per day), determined at the same time points. Using the collected data and the SIC scores, all patients with sepsis will be tested for SIC at least once a day. Additionally, SIC scores (exact scores) will be recorded daily until day 14 after sepsis onset or discharge from the ICU (whatever occurs first). The date and time of the first SIC occurrence will be registered. The data collected will also be used to calculate the severity of SAC, according to Lyons et al. [6]. Finally, until day 14 after the onset of sepsis, each patient will be checked for thromboembolic events and non-trauma or surgery-related major bleeding (causing a drop in hemoglobin of <1 g/dL) once a day. In addition, on the 28th day after sepsis onset, it will be determined whether cardiovascular events, thromboembolic events, or non-trauma or surgery-related major bleeding (causing a drop in hemoglobin of <1 g/dL) occurred during the second 14 days of follow-up monitoring (yes/no recording for the second 14 days). Figure 2 provides an overview of the planned timeline. The time frames were chosen on the basis of balancing efforts and benefits. Since it is currently assumed that SIC occurs in the early phase of sepsis due to a dysregulation of the interaction of the innate immune response with the coagulation system, a special focus was placed on the first days, i.e., day 0 (sepsis onset) and the following 4 days. The aim is to identify possible early warning signs of SIC. Sepsis is usually treated anti-infectively for 7–14 days. The first occurrence of SIC after day 14 was considered very unlikely. The experts involved in the study planning were of the opinion that the occurrence of SIC after day 14 was most likely due to a secondary infection (which triggers a new sepsis episode) or another sepsis-independent reason. It was decided to use the 28-day mortality rate, as it is frequently collected in sepsis studies and thus allows an approximate comparison of the mortality of this cohort with other study cohorts. In the aforementioned effort to balance efforts and benefits, it was decided to investigate the potential effects of SIC on thromboembolism and bleeding risk up to day 28.

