### 2.10. Statistical Methods

All patients who do not have SIC at the beginning of their individual observation period will be included in the calculation of the cumulative observation period for determining the incidence rate of SIC. The observation period for determining the incidence rate of SIC ends at the time of diagnosis of SIC or discharge from the ICU (depending on which event occurs first), but at the latest at the end of the 14-day observation period. The incidence rates for sepsis and septic shock are determined in the same way. To determine the incidence density, the number of incident patients is divided by the cumulative sum of the individual observation days of all patients included in the incidence calculation. The incidence density is thus calculated according to the following formula:$$\frac{\mathrm{Number}\;\mathrm{of}\;\mathrm{incidental}\;\mathrm{cases}}{\begin{array}{l} \mathrm{Sum}\;\mathrm{of}\;\mathrm{the}\;\mathrm{individual}\;\mathrm{observation}\;\mathrm{period}\;\mathrm{across}\;\mathrm{all}\;\mathrm{cases} \end{array}}$$

The corresponding 95% confidence interval is calculated based on a Poisson distribution. The incidence rates between the individual strata will be compared in pairs.

The point prevalences for SIC, sepsis, and septic shock will be determined on the first day of the observation period by calculating the ratio of the number of affected patients to the total number of patients in the ICUs on that day. The Wilson score method will be used to determine the associated 95% confidence interval. Using χ^2^ tests (or Fisher’s exact tests), the point prevalences of the individual strata will be compared. The prevalences of SIC, sepsis, and septic shock in the retrospective data collection will be determined analogously.

The available data will be described by specifying the median [interquartile range (IQR)] or the absolute (relative) frequency. Depending on the type of characteristic being analyzed, the different groups will be compared using the χ^2^ test (or Fisher’s exact test, if necessary), the Mann–Whitney U test, or the *t*-test. The Kaplan–Meier method will be used to determine survival times, and the log-rank test will be used for the relevant group comparisons.

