A logistic regression model will be used to investigate mortality and describe it using odds ratios (including the associated 95% confidence intervals). Only variables that prove to be significant in the univariate analysis will be transferred to a multivariate model.

Multivariate logistic regression will be performed to compare the survival of SIC-positive and SIC-negative patients while adjusting for age, sex, the use of anticoagulants, and the SIC-adapted SOFA score at sepsis onset (i.e., the time of sepsis diagnosis). To calculate the SIC score, the SOFA score will be adapted according to Iba et al. [4] (see also Table 1). Two-sided *p* values will be used.

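### The mortality comparison by SIC status does not say when SIC status is fixed, and on the natural ever-SIC reading the planned methods are biased in a direction that cannot be known beforehand

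*Protocol article*

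**What the plan says.** Section 2.10 of the protocol article states: "Multivariate logistic regression will be performed to compare the survival of SIC-positive and SIC-negative patients". The model is planned "adjusting for age, sex, the use of anticoagulants, and the SIC-adapted SOFA score at sepsis onset", so SOFA is tied to a time point and SIC status is not. The same section adds: "The Kaplan–Meier method will be used to determine survival times, and the log-rank test will be used for the relevant group comparisons". It does not list which groups are relevant, but section 2.4 makes mortality in the SIC and SAC subgroups a secondary outcome: "Mortality rate until day 28, hospital death, or hospital discharge", whichever comes first.

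Section 2.5 describes how SIC is ascertained: "SIC scores (exact scores) will be recorded daily until day 14 after sepsis onset or discharge from the ICU", whichever is earlier. It adds: "The date and time of the first SIC occurrence will be registered". INR and platelet count are listed for the day of sepsis diagnosis, days 1–4 and a discharge day. The day-28 check of other events runs from sepsis onset ("on the 28th day after sepsis onset, it will be determined whether cardiovascular events, thromboembolic events"). No sentence gives the time origin for mortality separately.

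Nothing in section 2.10 names a landmark, a time-dependent covariate or a rule for values taken shortly before death.

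**The concern.** The primary outcome is new SIC, so the study itself expects SIC to arise after sepsis onset. The mortality analysis then uses one label per patient, in methods that treat the label as known at time zero. If the label means SIC at any time up to day 14, three mechanisms act:

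- **Early death.** A patient who dies before SIC could appear stays SIC-negative. This adds deaths to the SIC-negative group and lowers the odds ratio.
- **Early live discharge.** Scoring stops when the patient leaves the ICU. A patient who leaves alive before SIC could appear also stays SIC-negative, which adds survivors to that group and raises the odds ratio.
- **SIC near death.** INR, platelets and SOFA may worsen because the patient is dying. Such patients move into the SIC group, or a worse SAC grade, and the odds ratio rises.

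Age, sex, anticoagulant use and SOFA at onset cannot correct a label that depends on later survival and stay. The reported SIC–mortality association could therefore look protective or harmful, or hide a real association, for reasons unrelated to SIC.

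**Working it through.** **The plan's own forecast.** Section 2.7 takes from the earlier study about 12,000 screened and 1500 septic patients in 133 ICUs over 4 weeks. INSIC aims at 150 ICUs for 2 weeks.

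- ICU patients: 12,000 × 150/133 × 2/4 = 6767 (stated about 6700).
- Sepsis: 1500 × 150/133 × 2/4 = 846 (stated about 850).
- SIC: 30–60% of 850 = 255–510 (stated 250–500).

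The forecast reproduces. It is used here only to set n = 850 and a SIC share inside 30–60%.

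**Assumptions that are not in the document.** SIC has no effect on death. The daily death hazard is 0.03 for 7 days and 0.01 afterwards, so survival to day 28 is s = exp(−(0.21 + 0.21)) = 0.657 and mortality is 34.3%. Of all septic patients, 40% are destined for SIC: a share p0 at onset and a share p1 spread evenly over the next W days. Alpha is 0.05 two-sided.

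**Step 1: ever-SIC, ICU discharge ignored.** The mean chance of being alive when SIC is due is a = (1 − exp(−0.03W))/(0.03W). This is 0.902 for W = 7 and 0.942 for W = 4. The ever-SIC share is P = p0 + p1·a. Every 28-day survivor destined for SIC is labelled, so:

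- SIC-positive: 0.4s survive, P − 0.4s die.
- SIC-negative: 0.6s survive, 1 − P − 0.6s die.
- OR = 1.5 × (P − 0.4s)/(1 − P − 0.6s).

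For p0 = p1 = 0.20 and W = 7: P = 0.3804. SIC-positive deaths are 0.3804 − 0.2628 = 0.1176 and SIC-negative deaths are 0.6196 − 0.3942 = 0.2254. OR = 1.5 × 0.1176/0.2254 = 0.78.

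| p0 / p1 | OR, W = 4 | OR, W = 7 | Chance of a false significant result at n = 850, W = 7 |
|---|---|---|---|
| 30% / 10% | 0.93 | 0.89 | 13% |
| 20% / 20% | 0.87 | 0.78 | 37% |
| 10% / 30% | 0.81 | 0.69 | 69% |

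**Step 2: add ICU discharge.** With an exponential ICU stay of mean 8 days and a post-ICU death hazard of 0–1% per day (both assumed), simulation with W = 7 gives ORs of about 0.95, 0.89 and 0.84, in the order of the table. The false-significance rates fall to about 6%, 10% and 16%. Across both windows the range is about 0.84–0.97.

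**Step 3: add SIC near death** (20%/20%, W = 7, no discharge). Deaths by day 14 are 1 − exp(−0.28) = 0.2442. Of these, 0.3804 − 0.4 × 0.7558 = 0.0781 are already SIC-positive, which leaves 0.1661. If a fraction f of these cross the SIC limit just before death:

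OR = 1.5 × (0.1176 + 0.1661f)/(0.2254 − 0.1661f)

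This gives 0.96, 1.18 and 1.43 for f = 10%, 20% and 30%. The OR passes 1 when 0.1176 + 0.1661f = 0.4 × 0.343 = 0.1372, that is at f of about 12%.

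**Step 4: other assumptions.** A second simulation used 25% or 40% mortality, constant or front-loaded hazards, and 45% latent SIC. With 20% SIC at onset and a mean ICU stay of 8 days, its ORs were 0.82–0.95. With no SIC at onset and discharge ignored they were 0.52–0.74. With 20% or 40% near-death conversion they were 1.07–1.19 or 1.53–1.66.

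**Step 5: status fixed in time.** Using status at onset, or a day-4 landmark among survivors, the same simulation returned 0.99–1.01. If all SIC is present at onset, the ever-SIC OR is also 1.00.

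**The case against.** The strongest reply is that ever-SIC is nowhere stated. Daily scoring serves the incidence outcome, the 72-hour recovery rate and the longitudinal course, and it need not define the exposure for mortality. The only time anchor in the regression sentence is sepsis onset. If onset status was meant, the bias disappears. A condensed article may also leave such a definition to the full protocol or analysis plan. The first part stands: a reader might infer that the plan commits to ever-SIC, and the text does not support that. The second stands only in part. The article names the model, the covariates and the timing of SOFA, and it leaves undated the one variable whose timing decides whether the named methods are valid.

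A second reply is that SIC is expected early. Section 2.5 puts its focus on days 0–4, and with discharge counted the bias is modest. That is fair and is reflected in the ranges above. But the timing of SIC is what the study sets out to learn, so the validity of the analysis should not depend on it.

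Third, the near-death crossing rates have no basis in the document. That is also fair: they show only that the sign can change.

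A reader might also infer that these associations are meant to justify or size later randomised trials. The Introduction and Discussion name incidence, spontaneous course and recovery for that purpose. No passage assigns that role to the mortality odds ratio.

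**Conclusion.** The point holds in a limited form. Section 2.10 fixes ordinary logistic regression and fixed-group survival methods on a SIC label without a time, while SIC is acquired over up to 14 days. On the ever-SIC reading the result is biased, and the net direction depends on how early deaths, early live discharges and near-death SIC balance.

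The size is uncertain. All odds ratios above rest on assumed hazards, SIC timing, ICU stay and crossing rates. The figures that ignore ICU discharge overstate the downward bias, because scoring does stop at discharge. If status at sepsis onset was intended, there is no bias and only the wording needs to change.

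The primary incidence rate and point prevalence are not touched, so this is a should-fix point on secondary associations. The same reasoning applies to SAC grade. It should not be inferred, however, that all SAC times are already available: an onset time is registered only for first SIC, and INR and platelets are listed only for days 0–4 and a discharge day, whose meaning for patients who die is unclear.

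**What to change.** State in section 2.10, or in the analysis plan before analysis, when SIC status and SAC grade are fixed for the mortality comparison:

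1. **Time point.** Use either status at sepsis onset or status at a prespecified early landmark, for example the end of day 2, with the end of day 4 as sensitivity analysis.
2. **Population and follow-up.** Run the planned adjusted logistic model and survival curves in patients alive and still in the ICU (still under SIC scoring) at that time. Count deaths from then to day 28.
3. **Sensitivity analysis.** Add a Cox model with SIC as a time-dependent covariate, using the registered time of first SIC. This handles early death before SIC. It does not by itself remove SIC that appears just before death.
4. **SAC.** Grade from the INR and platelet values of days 0–4, up to the chosen time point. Do not grade from the discharge-day or death-day value.

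The cost is wording and modest programming, with no new data. Onset status loses no patients but does not address SIC that develops later. A landmark removes earlier deaths: 1 − exp(−0.03 × 3) = 8.6% by the end of day 2, counting onset as day 0, under the assumed hazards. It also removes earlier discharges. With the assumed mean stay of 8 days, exp(−(0.03 + 1/8) × 3) = 63% remain at the end of day 2 and exp(−(0.03 + 1/8) × 5) = 46% at the end of day 4, or about 530 and 390 of 850. Earlier deaths and discharges, and SIC that starts after the landmark, should be described separately.

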### 2.11. Data Monitoring

To enable standardized data collection across all centers, the investigators are trained via video conferencing before the start of the study. In addition, written material and a frequently asked questions (FAQ) list are available for all investigators. Furthermore, regular video conferences are offered during the ongoing study to answer questions about the study process and data collection. The FAQ list will be updated regularly. Moreover, the RedCap database used automatically checks data plausibility (according to tables of plausible values stored in advance) and completeness. Automated queries and notes are issued to the user. However, as only data collected as part of standard patient care may be entered, queries due to missing data may be ignored by the investigators. Moreover, central monitoring is carried out by the staff of IMISE Leipzig. In the event of anomalies that indicate, e.g., systematic errors in data entry, the relevant study center is contacted. As this is a trial that is purely observational in nature, no professional monitoring is planned. All local investigators are invited to keep in close contact with the principal investigator (email, telephone, video call apps) to ensure that the trial is conducted according to the protocol and regulatory requirements. Based on the experience of the INSEP study, which used a very similar study protocol and was conducted to a large extent at the same study centers by the same people, a high compliance rate regarding data collection across participating study centers is expected [18].

### 2.12. Harms

Due to the purely non-interventional nature of the INSIC trial, study-related adverse events (AEs) are not to be expected.

### 2.13. Auditing

No scheduled audits by the sponsor are intended to be conducted. In cases where the relevant authorities need to conduct an on-site inspection or audit, the investigator must ensure the availability of all documents and support this work at any time.

### 2.14. Ethics

The study will be conducted according to SOPs designed to ensure that all involved parties abide by the principles of Good Clinical Practice (GCP) [22,23] and the Declaration of Helsinki [24]. Moreover, the INSIC trial will be carried out in accordance with local statutory and implementing provisions.

### 2.15. Approval of the Institutional Review Board

Patients will not be enrolled at each site until there has been approval from the relevant institutional review board (IRB). The first IRB to approve the study completion was the Ethics Committee of the Medical Faculty of the University Duisburg-Essen (Votum no. 21-9969-BO).

### 2.16. Protocol Amendments

Changes to the protocol must be made in writing and require the approval of all signatories of the protocol. Subsequent amendments also require a positive assessment from the relevant IRB.

### 2.17. Consent or Assent

The requirement for written informed consent was waived by the IRB, as in the INSIC trial only data collected during standard patient care are included. Moreover, all data processing will be anonymous, and prevalence and incidence calculations are only possible if all patients are included.

### 2.18. Confidentiality

All collected data will be handled in accordance with the provisions of the General Data Protection Regulation (GDPR) of the European Union and the European Council [25]. All data containing the identity of the patient will only be accessible to the attending doctors and nursing staff; for all other investigators involved in the study, this data is encrypted and will use a pseudonym. Only the investigators at the respective study site are able to assign a pseudonym to a patient’s name, and only for as long as needed to complete data collection. After the 28-day follow-up, the data sets will be completely anonymized so that decryption is no longer possible. All data that will be processed and used in subsequent publications will be strictly anonymous.

## 3. Discussion

SIC is significantly associated with increased morbidity and mortality [9]. Studies from Japan and China and also a subgroup analysis of the SCARLET (Sepsis Coagulopathy Asahi Recombinant LE Thrombomodulin) trial suggest a causal influence of coagulopathy on mortality [4,14,26]. Several studies on the possible effects of anticoagulation, using various compounds, have been undertaken in this area. In a retrospective study by Yamakawa et al., anticoagulation was clearly associated with reduced mortality, at least in patients with sepsis and overt DIC and in patients with a SOFA score of 13–18 [27]. A subgroup analysis of the SCARLET trial showed that the study drug thrombomodulin probably has a more pronounced positive effect when used only in patients with high thrombin fragment 1.2 levels [28]. In the SCARLET trial, 800 patients with severe sepsis (according to the sepsis-2 definition) and SAC were randomized; half of the patients received recombinant soluble thrombomodulin and the other half received a placebo [14]. The study failed to show a difference in its primary endpoint of 28-day mortality [14]. However, a subgroup analysis showed that in approximately 20% of the included patients, SAC had already resolved between the patients’ time of study inclusion and the time of the first administration of the medication [14]. When considering only the remaining 80% of patients who actually met the inclusion criteria when the study drug was first administered, the difference in survival is significant; however, the study was not powered for this setting. In this way, the SCARLET trial highlights problems that have probably contributed to the failure of a whole series of RCTs: [13,29,30,31]. We know too little about the incidence of sepsis-induced coagulopathies and too little about their spontaneous course and the factors that determine whether spontaneous recovery occurs or SIC contributes to morbidity and mortality. The INSIC trial is designed to provide new insights into the actual incidence and course of SIC. This may lay the foundation for more precise planning of interventional RCTs aimed at modulating coagulation in sepsis. The strength of our work lies in the large number of participating centers. Since so far only retrospective data on SIC prevalence in partly pre-selected groups are available [4,9,10,11,32], INSIC is intended to be the first to measure SIC incidence across a broad range of different patients with sepsis. In addition, the INSIC trial should provide insights into the proportion of patients who experience spontaneous recovery within the first 72 h of standard sepsis treatment (according to the guidelines of the Surviving Sepsis Campaign) [33]. However, we will also have to face some limitations. Firstly, it is expected that more university hospitals than small hospitals will participate. This could potentially lead to a bias towards more severe cases, but also towards more aggressive treatment. For example, difficult cases with a potentially good prognosis could be referred more often from smaller hospitals to university hospitals, where maximal therapy is provided, whereas smaller hospitals would more often continue to treat patients for whom, due to age for example, not all maximal therapeutic measures are desirable or indicated. However, this bias could also be an advantage in using the results of the INSIC trial to plan interventional studies, as these are traditionally conducted at university hospitals due to their need for human resources. Secondly, since we only request data collected as part of standard care, we are limited to the blood values that are typically measured. Rarely performed tests, such as thrombin fragment 1.2 or thrombin–antithrombin complex levels, will rarely be reported, meaning we will likely obtain only small sample sizes for these data. Overall, the INSIC trial is the first study to determine the incidence of SIC and to prospectively examine the course of SIC longitudinally over a 14-day period in a large sample size. This provides a sound basis for planning future RCTs.
